##### Primary outcomes

Tolerability will be assessed by checking vital signs regularly during the dosing sessions and recording AEs arising at any time during the study. AEs will be classified based on the type, number, severity, relatedness to the study drug, and whether the event constitutes a serious adverse event (SAE) or significant safety issue (SSI).

The feasibility of participating in physiotherapy during the acute effects of psilocybin 15 mg will be assessed by measuring the successful completion of a series of movement tasks. These will include the S-FMDRS (Nielsen *et al.,*
2017a), DEMMI (de Morton *et al*., 2008), FME, ARAT (Yozbatiran *et al*., 2008), and BBT (Mathiowetz *et al*., 1985) (original and modified versions) at 1.5 and 4.5 hours post-dosing.

The S-FMDRS assesses seven body regions and two functional movements (gait and speech) commonly affected by motor FND. Severity and duration are each rated from 0 to 3 for each of the nine items (higher scores indicate greater impairment), with items summed to provide a total score between 0 and 54. The scale may be completed by neurologists and physiotherapists, has high inter-rater reliability for the total score, and is sensitive to treatment-related changes. The assessment of the S-FMDRS by the study physiotherapist will comprise the primary outcome for assessing clinician-rated symptom severity. The S-FMDRS will be completed at baseline, 1.5 and 4.5 hours post-dosing for participants receiving psilocybin 15 mg, completion of the physiotherapy treatment, and the one-week and four-week follow-up visits.

The PGI-S and PGI-I are self-rated, single-item scales to capture static and dynamic aspects of disease severity and change, respectively (Food and Drug Administration, 2018). The PGI-S is rated from 1 to 4 (higher scores indicate greater impairment), and the PGI-I is rated from 1 to 7 (lower scores indicate greater improvement, and higher scores indicate worsening). These measures have shown satisfactory feasibility, validity, and sensitivity to treatment-related changes in studies on neuropsychiatric symptoms (Mohebbi *et al*., 2018; Snyder *et al*., 2021; Remigio-Baker *et al*., 2024). The PGI-S will be completed at baseline, and both scales completed on the morning of each day of the physiotherapy treatment and dosing session, following completion of the physiotherapy treatment, and at the one-week and four-week follow-up visits.

##### Secondary outcomes

An independent assessment of each S-FMDRS measure, as captured using video footage, will be completed by the study neurologist who will be blinded to treatment allocation. This will comprise a secondary outcome to help assess the interrater reliability and utility of this measure for this and subsequent studies. To complement the participant-reported PGI-I and PGI-S scales, the clinician-rated CGI-I and CGI-S (Busner & Targum, 2007) will be administered to objectively assess disease severity and change, respectively, post-treatment.

Depressive symptoms will be measured by the PHQ-9 (Kroenke *et al*., 2001), anxiety symptoms by the GAD-7 (Spitzer *et al*., 2006), somatic symptoms by the PHQ-15 (Kroenke *et al*., 2002), and health-related quality of life by the SF-36 (Ware *et al*., 1993). Treatment expectations will be assessed pre-dosing by the SETS (Younger *et al*., 2012), and intensity of the acute drug effects assessed post-dosing by the 5D-ASC (de Deus Pontual *et al*., 2023) and EDI (Nour *et al*., 2016).

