### Assignment of interventions

#### Allocation sequence

Participants will be randomised in a 1:1 ratio into one of the two treatment groups until 12 participants in each group have been allocated. The randomisation list will be computer-generated by an independent statistician of the University of Melbourne, using random block sizes, and uploaded as a randomisation module into Research Electronic Data Capture (REDCap) (Harris *et al*., 2009). After the study psychiatrist confirms eligibility, the study coordinator, who is independent of administering interventions, will action the randomisation module, allocating the treatment group.

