#### Blinding

The statisticians and an independent assessor of symptom severity will be blinded to treatment assignments and will not be permitted access to the randomisation module. Videos for independent assessment of symptom severity will be allocated via a random number generator. If there is an emergency requiring knowledge of a participant’s allocation, the blind may be broken for that individual participant.

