##### Psilocybin dosing session

The psilocybin dosing session will take place within three days of the initial physiotherapy sessions. Upon arrival, the study psychiatrist will ensure the participant’s continued eligibility and safety by reviewing their medications, measuring vital signs, and conducting a urine drug screen and urine pregnancy test (if applicable). The psychiatrist will then administer the prescribed psilocybin. The participant will be encouraged to relax, with the study psychiatrist available to provide support. Vital signs will be rechecked at 0.5-, 1, 3, and 5 hours post-dose, and AEs monitored throughout. For participants randomised to the moderate-dose arm, the physiotherapist will attend at 1.5 and 4.5 hours post-dose to administer a series of movement tasks and any further physiotherapy as tolerated by the participant to explore any potential treatment benefit of novel experiences of movement during the acute drug effects.

The participant will remain under the supervision of the study psychiatrist or physiotherapist for at least 5 hours post-dose and until the acute drug effects have subsided. The participant will then complete questionnaires regarding the intensity of their experience before being taken home by a support person or taxi. The psychiatrist will telephone the participant the following day to invite any further reflections and monitor safety.

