### Data management

The majority of study data will be collected and managed using REDCap (Harris *et al*., 2009) – a secure, browser-based application for managing online surveys and databases – hosted at the University of Melbourne. Scanned paper-based Case Report Forms (CRFs), video footage, recordings and transcripts of qualitative interviews, and fMRI images will be uploaded and stored in secure, password-protected servers hosted by the University of Melbourne and available only to permitted trial staff. Results from urine tests will be recorded, and urine samples will be disposed of in biological hazard waste bins.

Confidentiality will be maintained by assigning participants a unique code to record any data collected, and paper-based CRFs will be stored in locked filing cabinets. Videos of physiotherapy task performance will be de-identified using facial blurring, and qualitative interview audio recordings will be transcribed in a de-identified manner.

On study completion, scanned and electronic source documents will be archived on password-protected servers, and paper-based CRFs kept in locked cabinets. All CRFs will be retained for 15 years and then destroyed by secure shredding and deletion from protected servers according to the University of Melbourne records management policy.

Data management will be carried out to a standard of security and confidentiality consistent with Good Clinical Practice (International Council for Harmonisation, 2015). Data will be handled only by the research team and held at the Department of Psychiatry, University of Melbourne, Austin Health.

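### The blinded neurologist is to rate every S-FMDRS video, but dosing-session videos arise only in the 15 mg arm, which can compromise the blind

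*Protocol article*

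**What the plan says.** Secondary outcomes sets the scope of the independent rating: "An independent assessment of each S-FMDRS measure, as captured using video footage, will be completed by the study neurologist who will be blinded". The blind concerns which arm the participant is in. The rating applies to each measure, with no visit left out.

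Primary outcomes gives the timing: "The S-FMDRS will be completed at baseline, 1.5 and 4.5 hours post-dosing for participants receiving psilocybin 15 mg, completion of the physiotherapy treatment", then the one-week and four-week visits. Psilocybin dosing session confirms that the acute assessments belong to one arm: "For participants randomised to the moderate-dose arm, the physiotherapist will attend at 1.5 and 4.5 hours post-dose to administer a series of movement tasks". Trial design describes the 25 mg arm as having no such tasks at dosing.

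The stated protections are these:
- Blinding: the statisticians and the assessor "will be blinded to treatment assignments and will not be permitted access to the randomisation module".
- Blinding: "Videos for independent assessment of symptom severity will be allocated via a random number generator".
- Data management: "Videos of physiotherapy task performance will be de-identified using facial blurring".
- Study setting: physiotherapy sessions and follow-up visits share the dosing room.

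Secondary aims lists the video-rated S-FMDRS among the outcomes to be compared within and between groups. The primary S-FMDRS score comes from the study physiotherapist, who also delivers the treatment (Primary outcomes; Data collection and assessment).

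**The concern.** The scope of the rating and the claim of blinding do not fit together. A rater who receives every S-FMDRS video receives some that can come from only one arm. The scale covers seven body regions plus gait and speech, so the features that could identify a person across clips are the ones the rater must study closely.

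At stake is the between-arm comparison of the video-rated S-FMDRS. The treating physiotherapist's rating is openly unblinded, so the neurologist's rating is the trial's main protection against assessor bias on symptoms. If its blind fails unnoticed, the report will describe as blinded a comparison that the procedure did not keep blind. The loss cannot be undone, because a rater who has seen the dosing clips cannot be blinded again.

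**Working it through.** The plan gives no figure for this point. The check is a count of scheduled clips, followed by a calculation of what the clips disclose.

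**Inputs.** Twelve participants per arm: "Participants will be randomised in a 1:1 ratio into one of the two treatment groups until 12 participants in each group have been allocated" (from the section on the allocation sequence). S-FMDRS time points from Primary outcomes: four common to both arms (baseline, end of physiotherapy, one week, four weeks), plus two at dosing in the 15 mg arm only.

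**Step 1: clips in the rater's set, assuming every scheduled assessment is completed and filmed.**

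| | 15 mg | 25 mg | Total |
|---|---|---|---|
| Common visits | 12 × 4 = 48 | 12 × 4 = 48 | 96 |
| Dosing session | 12 × 2 = 24 | 0 | 24 |
| All | 72 | 48 | 120 |

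Dosing clips are 24/120 = 20% of the set.

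**Step 2: a recognised dosing clip.** P(15 mg | dosing clip) = 24/(24 + 0) = 1.

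**Step 3: the common-visit clips.** Let q be the chance that a 15 mg participant's dosing clip is recognised and linked to that person's other clips. The documents give no value, so q is an assumption and the whole range is shown. The rater guesses 15 mg if a dosing clip is linked and 25 mg otherwise, and is taken never to mistake a common-visit clip for a dosing clip.

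- Correct guesses = 0.5 × q + 0.5 × 1 = 0.5 + 0.5q
- P(15 mg | no dosing clip linked) = 0.5(1 − q) / [0.5(1 − q) + 0.5]

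| q | Correct guesses | P(15 mg), no dosing clip linked |
|---|---|---|
| 0 | 50% | 50% |
| 0.25 | 62.5% | 43% |
| 0.5 | 75% | 33% |
| 0.75 | 87.5% | 20% |
| 1 | 100% | 0% |

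**Step 4: missing dosing clips.** Sample size assumes 80% completion of physiotherapy during dosing. Its own figure reproduces: 1 − 0.8^12 = 0.931, in line with the stated chance above 90% of at least one non-completer. The expected number of non-completers is 12 × 0.2 = 2.4. If they left no dosing clip at all (an assumption, since a partial session may still be filmed), q would average at most 0.8, and correct guesses at most 0.5 + 0.5 × 0.8 = 90%.

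**Step 5: the safeguards.** Denying access to the randomisation module does not help, because the information is in the footage. Random allocation of videos can hide order and visit but leaves the one-arm clips in the set. Blurring hides the face but not build, gait or symptom pattern, and nothing says that the voice is masked. The shared room may stop the setting from marking a dosing clip, but it does not hide any visible drug effect. Together they lower q; nothing in the text makes it zero.

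**The case against.** The strongest reply is that this is a risk and not a demonstrated loss of blinding. Two things must happen: the rater must recognise a dosing clip, then connect it to the same person's other visits. Random allocation, facial blurring and the shared room all work against that. No passage says that the rater is told the time point, or that the effects of 15 mg can be seen on a blurred movement video, least of all at 4.5 hours. This stands, and it limits the point to what can happen.

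A reader might go further in three ways that the documents do not support:
- That the rating task reveals allocation outright. This holds only at q = 1.
- That participants without a dosing clip are identified as 25 mg by elimination. This fails if some 15 mg participants do not complete the tasks, and 24 dosing clips is a maximum.
- That the inter-rater reliability check is spoiled. Agreement depends mainly on the neurologist not knowing the physiotherapist's scores, and the dosing clips do not disclose those.

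It can also be said that the release order of videos belongs in a fuller protocol or video manual, and that the schedule figure is not available to show which assessments are filmed. Silence on release order alone would be no finding. Here, however, the article itself fixes both the scope and the blind, and the two conflict as written.

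Finally, the outcome is secondary, in a 24-person pilot that already acknowledges its open-label limits. That lowers the stakes but does not remove the stated between-group aim.

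**Conclusion.** The concern holds as a risk to the blind. Under the plan as written, up to 24 of 120 clips (20%) can come only from the 15 mg arm, and any one of them, if recognised, gives that participant's arm with certainty. The 96 common-visit clips are exposed only to the extent that the rater links them to the same person. Correct guesses of allocation then lie between 50% and 100%, and the documents do not allow a narrower range. The clip counts assume 12 per arm with complete, filmed assessments.

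The consequence is confined to the secondary between-arm comparison of the video-rated S-FMDRS, which is the only symptom rating described as blinded. Harm to the inter-rater check is not established. Because the remedy is cheap and works only before rating starts, it should be adopted.

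**What to change.** In the Blinding section, state that the neurologist rates in two batches.

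1. Baseline, end of physiotherapy, one week and four weeks, for all participants, in random order across participants and visits, with the visit hidden. These ratings are locked before anything else is released: 48 + 48 = 96 clips, four per participant in each arm.
2. The 1.5-hour and 4.5-hour clips, released only after that lock and reported as not blinded to arm.

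Add that only the first batch supports blinded between-arm comparisons, and amend Secondary outcomes to match. Leaving the dosing clips out of the blinded set, or giving them to a second rater, would also work; a second rater would add staff.

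The two-batch order needs no extra ratings or staff and changes no study procedure for participants. The cost is delay: common-visit ratings must be finished for all participants before any acute clip is rated, so the neurologist's acute ratings would not be ready for the planned interim summary at 12 participants.

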##### Exploratory outcomes

Video footage and individual scores for each of the DEMMI, FME, ARAT, and BBT (original and modified versions) will be assessed to explore the impact of psilocybin-assisted physiotherapy on several domains of motor function. Resting-state fMRI will be used to investigate alterations in large-scale brain networks and potential treatment mechanisms (Daws *et al*., 2022; Berkovitch *et al*., 2025). This will be complemented by a Bayesian belief updating fMRI task, which will assess changes in optimism bias and any underlying neuroimaging correlates (Sharot *et al*., 2011; Korn *et al*., 2014; Marks & Baines, 2017). This task has revealed differences between healthy subjects and patients with MDD and is of relevance given the hypothesised role of aberrant predictive processing in motor FND. Given previous findings of reduced sensory attenuation in motor FND, which may arise through related mechanisms, treatment-induced normalisation of sensorimotor performance using a force-matching task will also be assessed (Pareés *et al*., 2014). In line with previous studies demonstrating changes in personality following psychedelics, such as increased ‘openness’, and the relevance of these changes to therapeutic effects, personality traits will be measured via the BFI-2 (Soto & John, 2017). Subjective experiences will also be assessed by surveying participant perspectives on the intervention and conducting a qualitative interview following the treatment.

## Data collection, management, and analysis

### Data collection and assessment

The study physiotherapist will provide the physiotherapy treatment and physiotherapy follow-up visits, administer movement tasks, and assess symptom severity. The study neurologist will conduct independent assessments of the S-FMDRS, as captured using video footage. Qualified radiographers will conduct fMRI scans. The study psychiatrists will conduct the screening visit, preparation session, dosing session, post-dosing phone call, psychiatry follow-up visits, qualitative interview, and remaining scheduled measures at these visits. At all times, the study team member administering the assessment has full responsibility for the accuracy, completeness, and timeliness of all data captured.

### Data management

The majority of study data will be collected and managed using REDCap (Harris *et al*., 2009) – a secure, browser-based application for managing online surveys and databases – hosted at the University of Melbourne. Scanned paper-based Case Report Forms (CRFs), video footage, recordings and transcripts of qualitative interviews, and fMRI images will be uploaded and stored in secure, password-protected servers hosted by the University of Melbourne and available only to permitted trial staff. Results from urine tests will be recorded, and urine samples will be disposed of in biological hazard waste bins.

Confidentiality will be maintained by assigning participants a unique code to record any data collected, and paper-based CRFs will be stored in locked filing cabinets. Videos of physiotherapy task performance will be de-identified using facial blurring, and qualitative interview audio recordings will be transcribed in a de-identified manner.

On study completion, scanned and electronic source documents will be archived on password-protected servers, and paper-based CRFs kept in locked cabinets. All CRFs will be retained for 15 years and then destroyed by secure shredding and deletion from protected servers according to the University of Melbourne records management policy.

Data management will be carried out to a standard of security and confidentiality consistent with Good Clinical Practice (International Council for Harmonisation, 2015). Data will be handled only by the research team and held at the Department of Psychiatry, University of Melbourne, Austin Health.

### Adherence and retention

Before their study treatment, participants will receive a detailed appointment handout, which also reiterates pre- and post-dosing requirements and recommendations. Travel costs incurred for attending each study visit will be reimbursed, up to $50 per visit, and food and drink will be provided at the dosing session. No additional financial inducements will be provided. The psychiatry follow-up visits and qualitative interview will be offered either in person or via video call, as per participant preference, to promote retention by reducing the required number of in-person visits. The study team will monitor data in real time to ensure completeness and will document attempts to obtain follow-up data and any protocol deviations.

To assess the fidelity of the physiotherapy treatment (the extent to which the treatment followed the intervention protocol):The study physiotherapist will complete a checklist for each participant, based on the template for intervention description and replication (TIDieR) checklist description (Hoffmann *et al*., 2014).The content, length, and number of physiotherapy sessions by participant report will be monitored with a structured telephone survey following completion of the physiotherapy treatment.A random sample of completed physiotherapy workbooks will be assessed by an independent physiotherapist against predetermined criteria.

### Statistical methods

Prior to the study database being locked, a comprehensive statistical analysis plan will be finalised. The analysis will encompass all participants who were randomised, regardless of whether they completed their full study enrolment. All available data from these participants will be included. The reasons for any participant’s early withdrawal from the study will be documented.

An interim analysis using unblinded data will be performed after 50% (*n* = 12) of the target sample size has completed their study enrolment. This analysis will consist of summary statistics of tolerability and efficacy outcomes by treatment groups. These interim results will support planning for a follow-up RCT in motor FND participants. As such, the goal of the interim analysis is not related to this pilot study, and no sample size adjustment will be made as a result. Blinding will be maintained as described earlier.

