### Trial design

This is a two-arm, individually randomised parallel-group study in 24 participants with refractory motor FND who will be randomly assigned, in a 1:1 ratio, to one of two treatment groups:Psilocybin 15 mg with movement tasks during the acute drug effects (moderate-dose arm), orPsilocybin 25 mg without movement tasks during dosing (standard-dose arm).

All participants will receive specialist, FND-specific physiotherapy, including two sessions pre- and six sessions post-dosing. Physiotherapy follow-up visits will occur one week and four weeks after completing their treatment. Psychiatric oversight will be provided, including a preparation session before their psilocybin dose, supervision during the dosing session, and follow-up sessions one week and four weeks after completing their physiotherapy treatment. An overview of this design is outlined in Fig. 1. Statisticians and an independent assessor of symptom severity will remain blinded to treatment allocation.

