### Sample size

A sample size of 12 has been chosen because, assuming an 80% chance of a participant successfully completing physiotherapy during acute dosing, this provides over a 90% chance of enrolling at least one participant who is unable to complete the intervention. We consider a completion rate of at least 80% to be tolerable, and so a sample size of 12 is likely sufficient to screen for a poorly tolerated intervention. Participants who withdraw before psilocybin dosing will be replaced.

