##### Treatment

Participants will then be scheduled for their study treatment. This will comprise two initial physiotherapy sessions, the psilocybin dosing session, and then six physiotherapy sessions within three weeks post-dosing.

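### Allocation stops at 12 allocated per group although pre-dose withdrawals are to be replaced, and the single all-randomised population does not fit outcomes that only dosed participants can supply

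*Protocol article*

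**What the plan says.** Three statements bear on who counts.

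- Allocation sequence gives the stopping rule: "Participants will be randomised in a 1:1 ratio into one of the two treatment groups until 12 participants in each group have been allocated". Trial design gives the total: "This is a two-arm, individually randomised parallel-group study in 24 participants".
- Sample size: "Participants who withdraw before psilocybin dosing will be replaced". The same paragraph justifies 12 by assuming that 80% complete physiotherapy during acute dosing, which gives a chance above 90% of seeing at least one non-completer. It calls a completion rate of 80% or more tolerable.
- Statistical methods: "The analysis will encompass all participants who were randomised, regardless of whether they completed their full study enrolment", followed by "All available data from these participants will be included". No other population is named. A full analysis plan is due before database lock.

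A person can be randomised and never dosed. The allocation step is described as follows: "After the study psychiatrist confirms eligibility, the study coordinator, who is independent of administering interventions, will action the randomisation module, allocating the treatment group". Treatment then starts with physiotherapy: "This will comprise two initial physiotherapy sessions, the psilocybin dosing session, and then six physiotherapy sessions within three weeks post-dosing". On the dosing day there is a further check, in which "the study psychiatrist will ensure the participant’s continued eligibility and safety by reviewing their medications", with a urine drug screen and, where applicable, a pregnancy test.

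Primary outcomes defines feasibility as completing movement tasks at 1.5 and 4.5 hours after the 15 mg dose. Tolerability rests on vital signs during dosing and on adverse events (AEs), which Table 2 describes as treatment-emergent.

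**The concern.** The stopping rule counts allocations, while the replacement rule and the sample size argument count people who reach dosing. These agree only if nobody is lost between allocation and dosing, and the replacement rule exists because some loss is foreseen. Once a group has its twelfth allocation, a later pre-dose withdrawal in that group needs a thirteenth, which the stopping rule does not allow. The site must then either leave the group short of 12 dosed or exceed the stated allocation.

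If it exceeds the allocation, the second difficulty appears. The one stated population keeps the replaced person. Someone never dosed has no dosing vital signs and no task results, and is not exposed to drug-related AEs. Counted in a denominator, that person pulls the completion rate down and the AE rate down, so the treatment looks both less feasible and safer than it was among those who received it. With about 12 per arm, one or two such people are enough to matter, and the results are meant to inform a follow-up trial.

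**Working it through.** **Inputs from the protocol.** 12 per group; assumed completion 0.80, so non-completion 0.20; stated chance above 90%; tolerable completion 80% or more. No pre-dose withdrawal rate is given, so a range of 5% to 20% is assumed below.

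**Step 1: reproduce the plan's figure.** P(at least one non-completer among n dosed) = 1 − 0.8^n. For n = 12: 1 − 0.0687 = 0.9313. The stated figure is correct for 12 dosed.

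**Step 2: stop at 12 allocated, no slot for a replacement.** The n in the formula is then the number dosed.

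| Never dosed | Dosed | 1 − 0.8^n |
|---|---|---|
| 0 | 12 | 0.931 |
| 1 | 11 | 0.914 |
| 2 | 10 | 0.893 |

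At least 11 must be dosed for the stated figure to hold. Two unreplaced withdrawals in the 15 mg arm break it, by a small margin.

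**Step 3: how likely are two or more?** With assumed pre-dose withdrawal w, P(two or more never dosed among 12) = 1 − (1 − w)^12 − 12w(1 − w)^11. For w = 5%, 10%, 15% and 20% this is 0.12, 0.34, 0.56 and 0.73.

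**Step 4: replace, and count everyone randomised.** With 12 dosed, k replaced and c completers, completion is c/12 among the dosed and c/(12 + k) among the randomised, if never-dosed people count as non-completers. The counts are illustrative.

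| Completers | Dosed only | k = 1 | k = 2 |
|---|---|---|---|
| 10 | 10/12 = 83.3% | 10/13 = 76.9% | 10/14 = 71.4% |
| 11 | 11/12 = 91.7% | 11/13 = 84.6% | 11/14 = 78.6% |
| 12 | 12/12 = 100% | 12/13 = 92.3% | 12/14 = 85.7% |

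With 10 completers, one replaced withdrawal takes the rate below 80%. With 11 it takes two. With 12 it takes four (12/15 = 80.0%, 12/16 = 75.0%).

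**Step 5: AE rates under the same counting.** Six of 12 dosed with an AE is 50.0%. Over all randomised it is 6/13 = 46.2% or 6/14 = 42.9%, if the never-dosed are counted as free of AEs.

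**The case against.** The strongest reply is that the protocol never states a denominator. It uses all available data, and a never-dosed person has none from the dosing session. Completion is defined during acute dosing, and AEs are treatment-emergent. Each of these allows a dosed-only denominator, and outcome-specific analysis sets are commonly left to the analysis plan, which is still to come. This stands: a reader might infer that the plan puts never-dosed people into the tolerability and feasibility denominators, but the text does not say so. That is only what its one unqualified population would mean if applied literally.

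Other strong readings also go too far.

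- A reader might see three rules in mutual contradiction. Replacing withdrawals and analysing all randomised can coexist. The literal conflict is between the stopping rule and the replacement rule.
- A reader might infer that replacement hides withdrawals. Statistical methods says that reasons for early withdrawal will be documented, and keeping all randomised keeps those people visible. Reporting by arm is simply not promised.
- A reader might infer that allocation comes too early, for example before any medication wean, and should be moved. The text ties it only to confirmed eligibility, and Contraindicated medications words its restrictions as conditions of enrolment. The documents show no error in the timing.
- The 80% figure belongs to the sample size reasoning. No decision rule is attached to it.

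The reply does not remove the conflict over allocation. That governs recruitment, and an analysis plan due only before database lock may come after recruitment has ended. Nor does it make the stated population fit the dosing-session outcomes. An analysis plan that adopted a dosed set would have to qualify the protocol's sentence.

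**Conclusion.** The point holds in limited form. The stopping rule and the replacement rule conflict when read literally, and the sample size argument supports a count of dosed participants. The effect on the plan's own figure is small: 93.1% with 12 dosed, 91.4% with 11, and 89.3% with 10, the first value below the stated level.

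The population sentence fits the tolerability and feasibility outcomes poorly. Its effect depends on the assumed numbers of withdrawals and completers, and on never-dosed people being counted as non-completers or as free of AEs. Under those assumptions one replaced withdrawal can lower completion by about 6 percentage points (83.3% to 76.9%) and an AE rate by about 4 (50.0% to 46.2%). Task completion is affected in the 15 mg arm only; tolerability is affected in both arms.

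**What to change.** 1. **Allocation sequence:** continue randomisation until 12 participants per group have been dosed, with allocation continuing for replacements. State how a replacement draws an allocation, since handing over the withdrawn person's arm would make that allocation known in advance.
2. **Statistical methods:** use dosed participants for vital signs and AEs, and dosed 15 mg participants for task completion. Keep all randomised for the symptom comparisons.
3. **Reporting:** give the number of pre-dose withdrawals, with reasons, by arm. List separately any AE in a person who was never dosed, since AEs are recorded throughout the study.

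The cost is wording, plus a randomisation list with spare entries and possibly a few more allocations than 24, which the replacement rule already accepts. Under the assumed withdrawal of 5% to 20%, the expected number randomised per arm is 12/(1 − w), that is 12.6 to 15.0, or 25.3 to 30.0 in total. With 12 dosed per group the plan's own figure stays at 93.1%.
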